### Secondary outcomes

#### Heart rate (HR)

Heart rate, a general index of arousal due to for examples stressful conditions, is influenced by both the parasympathetic and the sympathetic nervous system. Heart rate is usually measured in beats per minute (bpm), using the R-peak of the QRScomplex as a marker. The time between two R-peaks is measured over a given period of time, resulting in a RR-interval (or NN-interval, referring to normal beats). We will compute the level of HR in response to the trauma script.

#### Pre-ejection period (PEP)

The pre-ejection period (PEP) is defined as the time interval from the beginning of electrical stimulation of the ventricles to the opening of the aortic valve. PEP is an indicator of the sympathetic nervous system activity, which is high under stressful conditions [35]. We will compute the level of PEP in response to the trauma script.

#### Other measures

The SCID-5 is a semi-structured interview for DSM-5 Axis I disorders [41]. In this study, we administer three modules during screening: the Trauma and Stressor-Related Disorder to diagnose PTSD, Psychotic and Associated Symptoms, and Substance Use Disorders Modules, using the Bahasa Indonesian version of the SCID-5 [42].

Details of assessment instruments and time points are found in the Standard Protocol Items: Recommendations for International Trial (SPIRITS) Checklist (see Table 1). Other symptoms (PCL-5, HSCL-25, PSS) and quality of life (WHOQOL-BREF) will be measured at every time point at T0 (baseline), T1 (post-treatment), T2 (1 month follow-up), and T3 (3 months follow-up). We also administer the PCL-5, HSCL-25, PSS, and WHOQOL-BREF after a session of treatment.

**Table 1 Tab1:**
[figure not shown]
The schedule of enrollment, interventions, and assessments

The PCL-5 is a self-report 20-items questionnaire to assess the 20 DSM-5 symptoms of PTSD on a scale from 0 to 4 (“not at all (0)” to “extremely (4)”). Items are summed to provide a total severity score and total score range between 0 and 80. PCL-5 scores exhibited strong internal consistency (*α* = 0.94), test-retest reliability (*r* = 0.82), and convergent (rs = 0.74 to 0.85) and discriminant (rs = 0.31 to 0.60) validity in a study in trauma-exposed college students [43]. We use the Indonesian version of the PCL based on the DSM-5 [44].

The Live Events Checklist (LEC) will be used to assess which traumatic event(s) participants have experienced. The LEC has strong convergence with measure of psychopathology that are known to be associated with trauma exposure [45]. The LEC assesses exposure to 16 events known to potentially result in PTSD or distress and includes one additional item assessing any other extraordinarily stressful event. The participants rate their experience of the events on a 5 point nominal scale (1 = happened to me, 2 = witnessed it, 3 = learned about it, 4 = not sure, and 5 = does not apply), and they may endorse multiple levels of exposure to the same trauma type. The LEC does not yield a total score or composite score.

The Hopkins Symptoms Checklist-25 (HSCL-25) is used to measure anxiety and depression symptoms. The HSCL-25 consists of two parts: anxiety symptoms (10 items) and depression (15 items). Symptoms are scored on a five-point scale varying from “not at all (0)” to “extremely (4),” and total scores range between 0 to 40 for anxiety and 0 to 60 for depression, with higher scores indicating more symptoms. The HSCL-25 has been translated and culturally adapted for use in Indonesia [46]. The HSCL-25 is reliable and valid across a variety of cultural groups, including Indonesia [47].

The Perceived Stress Scale (PSS) is the most widely used instrument for measuring perceived feelings and thought of stress during the last month [28]. The PSS is one of the most widely used and established validity and reliability [48]. The PSS consists of 10 items on a scale from 0 to 4 (0 = never, 1 = almost never, 2 = sometimes, 3 = fairly often, 4 = very often). The PSS has been translated into Indonesia language. The reliability measure for PSS-10 using the Cronbach alpha was 0.84 [49].

Quality of life will be assessed using the World Health Organization Quality of Life (WHOQOL-BREF) [29]. The instrument consists of four domain scores and two other items measuring the overall perception of quality of life and general health during the past 4 weeks. The domains are grouped into physical health (7 items), psychological (7 items), psychological health (6 items), social relationships (3 items), and environment (8 items). Domain scores are scaled in a positive direction (1 = not at all, 2 = not much, 3 = moderately, 4 = a great deal, 5 = completely). The scores are transformed into a linear scale between 0 and 100, with lower scores indicating lower levels of quality of life. The WHOQOL-BREF has showed adequate psychometric properties across many contexts and across many health conditions in many countries [50, 51]. We will use Indonesian version of the WHOQOL-BREF [50].

#### Neurocognitive functioning

The neurocognitive instruments will be administered at baseline (T0), post-treatment (T1), one month (T2), and 3 months follow-up (T3). Wechsler Adult Intelligence Scale-Fourth Edition (WAIS-IV) has been validated and is commonly used embedded performance validity tests (PVTs) [52]. The WAIS-IV-ID (Indonesian version) has been adapted and validated by Suwartono et al (2014) [53, 54]. To assess attention and working memory, we administer the Digit Span subtest, a 3-part test involving digit span forward, backward, and sequencing [55]. Digit span forward is a test involving, attention, encoding, and auditory processing. Digit span backward will measure working memory, transformation of information, mental manipulation, and visuospatial imaging. Digit span sequencing was designed to measure working memory and mental manipulation of information.

The California Verbal Learning Test (CVLT) is a five-trial learning task, followed by an interference list and short delay free recall which measures encoding, short-term retrieval, and recognition of verbal information [56]. Participants are asked to recall a number of words in A list (immediate free recall), words in B list (immediate free recall), and last words in A list (short delay free recall) [57]. The CVLT second edition was translated and culturally adapted to Indonesian Multiple Sclerosis patients [58]. Estiasari et al. reported CVLT is valid and reliable and can be widely used to assess cognitive function in Indonesian participants [58].

The Trail Making Test (TMT) measures information processing speed, shift of attention, planning, and cognitive flexibility [59]. The TMT comprises of a part A and part B. In part A, the participant uses a pencil to connect a series of 25 encircled numbers in numerical order. In part B, the participant connects 25 encircled numbers and letters in numerical and letters. The administration time will generally range from 5 to 10 min [30]. The study results suggest that TMT A and B demonstrated adequate validity and reliability for assessing executive function and visuospatial processing speed among older adults [60, 61].

### Intervention

#### EMD treatment protocol

The procedures of EMD intervention will be carried out in line with the standard EMDR protocol [62]. Since we aimed to evaluate the effects of eye movement during retrieval of a traumatic memory, we decided to omit the installation phase from the original EMDR procedure in both study groups. It has been suggested that the installation phase may be counter-effective, since performing eye movements when retrieving a positive cognition or image (as done in the installation phase) may render that positive image less vivid and positive [9]. EMD will be given during 4 to a maximum of 6 sessions, and each session lasts 45–60 min. The therapist will provide at least 4 sessions, even if their Subjective Units Distress (SUDs) scores decrease to 0 or 1 in less than 4 sessions and stop when SUDs = 0 or 1 for all target memories. If the participant does not reach 0 or 1 in 6 sessions, the therapy will be ended nevertheless, to minimize heterogeneity. In addition, reductions in distress may also take place after the therapy has ended. SUDs measure the level of distress before and after target memory processing, where 0 is no disturbance or neutral and 10 is the highest disturbance.

EMD consists of the following steps: *(1) Client History* and *treatment planning*: obtaining information regarding the clients’ clinical condition, including intrusive emotions and physical sensations. *(2) Preparation*: building a therapeutic bond with the client, the explanation of EMDR process and its effects. *(3) Assessment*: identification of the target visual image of the traumatic memory and associated negative emotions. The participant describes the intensity of the negative emotions on a 0–10 SUDs scale). *(4) Desensitization*: clients will be asked to focus on target traumatic events, while focusing their eyes on the therapist’s finger that moves from left to right an back in the participant’s visual field. The therapist will conduct EM for 24 cycles several times. This phase will end if SUD scores reach 0 or 1. Next, participants will scan their body until any tension disappears. *(5) Closure*: the session is closed, and the stabilization techniques and relaxation exercises are reviewed. Sessions 2–4 will start with a reevaluation of the patient’s progress and SUD scores of target events to guide the choice of continuing with the target traumatic event or choosing a new event.

The EMD treatments will be performed by experienced psychotherapists with at least 1 year of experience in treating PTSD patients. Eight therapists are recruited through colleagues from the Clinical Psychologist Association (IPK). An accredited EMDR supervisor will supervise therapists weekly.

#### Retrieval-only condition (control)

Control participants will receive the same treatment as the EMD group participants, except that during phase *(4) Desensitization*, no eye movements will be performed during retrieval of the trauma memory.

#### Data collection, quality control, and confidentiality

All data will be pseudo-anonymized. A coding list with participant numbers and names, and the informed consent forms, will be stored in a separate locked place at the research coordinator’s office. Data are stored in the Castor Data Management program.

Drop out and premature termination from study or treatment at any point after randomization will be recorded. The participants can choose to withdraw from the trial intervention, withdraw from follow-up, withdraw from both conditions, and ask that previously collected data not be used. A participant may be withdrawn from intervention if he/she feels does not fit into the given intervention technique (e.g., the participant feels nauseous doing eye movements task when recalling the memory). Participants who withdraw from the intervention as part of the trial will proceed to the follow-up assessment unless they withdraw consent for this. For any participant reluctant to complete the full outcome assessment at follow-up, we will attempt to obtain the PCL-5, PSS, HSCL-25, WHOQOL-BREF, CVLT, Digit Span (WAIS-IV), and TMT. As much information as possible will be collected from protocol non-adherents including reasons for non-adherence. All randomized participants will be included in the intention to treat analysis.

#### Protection and assessment of safety

The study has been approved locally by the Health Research Ethics Committee of Medical Faculty of Padjadjaran University (KEPK-FK Unpad) on 26 June 2018. Adverse events (AEs) will be reported to KEPK-FK Unpad by the principal investigator.

#### Sample size

We expect that HRV will decrease in both groups at T1 compared with T0, with a smaller decrease in the EMD group, resulting in greater HRV at T1 in the EMD group compared with the EMD retrieval-only control group. No studies have been carried out yet comparing the effect of EMD to retrieval only on HRV in PTSD patients to inform power calculations. However, based on the theoretical assumptions and studies with other related outcome measures [63, 64], we expect to detect a difference between the EMD condition and retrieval only on HRV of a medium effect size (Cohen’s *d* = 0.4). Power calculations were conducted using G*power software and were based on based on a general linear model (GLM). Linear mixed-effect model can be conceptualized as GLM (repeated measure ANOVA) as a balanced design within independent sampling units, and an unstructured covariance model is assumed [65]. We transformed for Cohen’s *d* = 0.4 into *f* = 0.2. For a 2 between (treatment EMD conditions) X 2 within (baseline, post-treatment) repeated measure ANOVA (*α* = 0.05, power = 0.9, correlation between measures = 0.4, and medium effect-size *f* = 0.2) [7, 66]. A power calculation suggested that a total sample size of *N* = 82 will be required, which is 41 per condition. All power computations were conducted in the G*Power software. Considering drop out of participants, we will recruit an additional 25% extra participants, yielding a total number of 55 participants per condition, thus 110 participants in total.

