#### Statistical analysis

Baseline sociodemographic and outcomes of interest are first compared across treatment conditions. Data will be described by reporting results from general descriptive analysis. The categorical variables will be summarized as numbers and percentages and continuous variables as means and standard deviations, minimum, and maximum.

Following this, intention-to-treat analysis will be performed only for the primary outcome, and then performing multiple imputation with a sensitivity analysis using both observed and imputed data. *P* values of < 0.05 will be considered significant.

Statistical analysis will be conducted using R Statistics software. The stress reactivity outcome variables were measured only at T0 and T1. HRV is a primary outcome that is a continuous dependent variable. We will analyze our data using repeated measures analysis of variance (ANOVA) to examine the interaction between time (pre-post intervention), within-subject factor, and the between-group factor treatment group. This analysis allows us to compare the two groups over time to examine whether participants in the EMD condition benefit more in terms of stress reduction, when compared to the retrieval-only condition, from baseline to post-treatment.

We will analyze the secondary outcomes (self-report and neurocognitive measures) using linear mixed models, with a random effect for participants. Data from time points T0, T1, T2, and T3 will be included in the repeated measures models. In all analyses, a treatment × time interaction term will represent the effect of EMD and EMD retrieval-only interventions of the outcome variables over time. Trauma type, gender, and age will be included as covariates in all models, both for the primary as well as the secondary outcome(s).

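### Sample size: d = 0.4 is converted to f = 0.2 by the two-independent-groups rule, so the stated 90% power for the group-by-time interaction is about 37%

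*Protocol article*

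**What the plan says.** All inputs are in the Sample size section of the protocol article. It expects HRV to fall in both arms between T0 and T1, less so with EMD, and sets the difference between arms at Cohen's d = 0.4. It continues: "We transformed for Cohen’s *d* = 0.4 into *f* = 0.2". The design entered in G*Power is a 2 (between) × 2 (within) repeated measures ANOVA with α = 0.05 and "power = 0.9, correlation between measures = 0.4, and medium effect-size *f* = 0.2". The result is "A power calculation suggested that a total sample size of *N* = 82 will be required, which is 41 per condition". For dropout, "we will recruit an additional 25% extra participants, yielding a total number of 55 participants per condition, thus 110 participants in total".

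The Statistical analysis section fixes the primary test as a repeated measures ANOVA "to examine the interaction between time (pre-post intervention), within-subject factor, and the between-group factor treatment group". The Primary outcome section agrees: the expected contrast is a difference between arms in the change in HRV (RMSSD) from T0 to T1.

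**The concern.** Cohen's f is the standard deviation of the relevant effects divided by the within-cell standard deviation. For two independent means that differ by d SD, each mean lies d/2 from their average, so f = d/2. An interaction in a 2 × 2 table is spread over four cells, and the same difference gives cell effects half as large. Using d/2 in an interaction calculation therefore doubles the assumed effect and leaves the sample size about four times too small.

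The stake is the power claim for the primary outcome. Readers are told that the trial has a 10% chance of missing d = 0.4. If the true chance is above one half, a non-significant result says little about whether eye movements reduce stress reactivity, yet the published 90% would invite a firmer reading.

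**Working it through.** **Inputs** (Sample size section): d = 0.4; f = 0.2; correlation ρ = 0.4; α = 0.05; power 0.90; N = 82; 25% dropout; 110 recruited. Allocation is 1:1 (Randomization section). Number of groups k = 2, number of measurements m = 2.

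**1. Reproducing the plan's figure.** The G*Power routine for a within-between interaction uses λ = f²·N·m/(1 − ρ), with 1 and N − 2 degrees of freedom.

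- f = 0.2, N = 82: λ = 0.04 × 82 × 2 / 0.6 = 10.93, power 0.904.
- f = 0.2, N = 80: power 0.897, so 82 is the smallest even N that reaches 90%.
- Other routines do not give 82: the between-factor test in the repeated measures design gives 186, a one-way two-group test with f = 0.2 gives 266, and the interaction at α = 0.10 gives 66.
- Dropout: 41 / (1 − 0.25) = 54.7, rounded up to 55 per arm, 110 in total. This also reproduces.

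So the interaction routine was used, with f = 0.2.

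**2. The f that corresponds to d = 0.4.** Take SD = 1. Randomisation makes the expected baselines equal, and a change common to both arms cancels. The cell means can then be written as control (0, 0) and EMD (0, d). After removing row, column and grand means, every cell has an interaction effect of ±d/4. Their root mean square is d/4, so f = 0.4/4 = 0.1. Conversely, f = 0.2 corresponds to a difference in change of 4 × 0.2 = 0.8 SD.

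**3. Power with f = 0.1.**

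| Evaluable N | λ | Power |
|---|---|---|
| 82 | 0.01 × 82 × 2 / 0.6 = 2.73 | 0.372 |
| 110 | 0.01 × 110 × 2 / 0.6 = 3.67 | 0.475 |
| 318 | 0.01 × 318 × 2 / 0.6 = 10.6 | 0.90 |

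With 82 evaluable participants, the difference in change detectable with 90% power is about 0.79 SD.

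**4. Check by another route.** With two time points the interaction test is a two-sample t test on change scores. Their SD is √(2(1 − 0.4)) = 1.095, so the standardised difference is 0.4/1.095 = 0.365 and the noncentrality is 0.365 × √(82/4) = 1.65, whose square is 2.73. Power is again 0.372. A simulation of 20,000 trials with 41 per arm gave 0.373 for a difference of 0.4 SD and 0.903 for 0.8 SD.

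**5. Sensitivity.**

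- *d in change-score SDs.* The plan does not say which SD it uses. On this reading f = 0.4 × 1.095/4 = 0.1095; power is 0.432 at 82 and 0.547 at 110, and 90% needs 266.
- *Higher correlation.* With f = 0.1 and N = 82, power is 0.637 at ρ = 0.7, and 90% needs ρ of about 0.85. With 110 evaluable, ρ = 0.8 gives λ = 0.01 × 110 × 2 / 0.2 = 11.0 and power of about 0.91. The plan assumes 0.4.
- *Covariates.* To raise λ from 2.73 to 10.93, a factor of 4, trauma type, gender and age would have to remove about 75% of the change-score variance.
- *Baseline-adjusted ANCOVA* (not the planned analysis): residual SD √(1 − 0.4²) = 0.917; power 0.497 at 82 and 0.621 at 110.

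**6. Scale, for illustration only.** The Primary outcome section quotes a population RMSSD of 29.7 ± 18.1 ms. Assuming that SD also applies in this trial, which the plan does not say, 0.4 SD is 0.4 × 18.1 = 7.2 ms and 0.8 SD is 14.5 ms, about half the quoted mean.

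**The case against.** The best defence has four parts.

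- *The 37% rests on two conditions:* d in SDs at a single time point, and the full 25% dropout. The plan leaves the SD undefined and intends to randomise 110 and analyse by intention to treat with multiple imputation. This stands as a reason to show the range of 37% to 55%. It also means that the stated effect is not more likely missed than found under every reading: 55% is just above one half. But the plan attaches its 90% to 82 participants, so the figures to set against it are 37% and 43%. The single-time SD is the natural reading, because the section describes the effect as higher HRV at T1 and gives the correlation separately.
- *f = 0.2 may have independent support,* since references are attached to the G*Power inputs. They cannot be checked here. The text itself says that f was obtained from d = 0.4, and that no earlier study compares these two conditions on HRV in PTSD patients. The remedy should still leave this route open.
- *f = 0.2 would be right if the arms moved 0.4 SD in opposite directions.* The plan rules this out by expecting HRV to fall in both arms.
- *Neither the validity of the test nor the effect estimate is affected,* and the document does not say how a null result would be read. Both points are true. They limit the consequence to the power claim and to what a null result can support; they do not make the claim correct.

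**Conclusion.** The concern holds. The plan's arithmetic is reproducible, but the effect size entered is twice the one stated. On the plan's own α, correlation and d, power with 82 evaluable participants is about 37%, not 90%, and 48% if all 110 are evaluable. With d in change-score SDs the figures are 43% and 55%. A 90% claim for d = 0.4 would need 318 evaluable participants (266 on the second reading); what 82 supports at 90% is a difference in change of about 0.8 SD.

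These figures assume equal expected baselines, equal variances at T0 and T1, ρ = 0.4 and no gain in precision from covariates. A much higher correlation would narrow the gap, but the plan offers no support for one. This must be corrected, because it is the stated power for the primary outcome.

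**What to change.** In the Sample size section:

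- State which SD d = 0.4 refers to, and convert it for the interaction: f = d/4 = 0.1 for the single-time SD, or 0.1095 for the change-score SD.
- Restate the consequence: 82 evaluable participants give about 37% power for d = 0.4 (43% on the change-score reading), 110 give 48% (55%), and 82 give 90% power for a difference in change of about 0.8 SD.
- If f = 0.2 was in fact intended, say so, drop the derivation from d = 0.4, and justify a difference in change of 0.8 SD.
- State that a non-significant result does not exclude d = 0.4, and that the confidence interval for the difference in change will be reported so that readers can see what is excluded.

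Optionally, give the ANCOVA figures alongside (50% at 82, 62% at 110; about 0.66 SD detectable with 90% power at 82), labelled as a different analysis from the one planned.

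The cost is rewording one section and accepting a less favourable power statement. No change to enrolment, data collection or the primary test is required.

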#### Statistical analysis

Baseline sociodemographic and outcomes of interest are first compared across treatment conditions. Data will be described by reporting results from general descriptive analysis. The categorical variables will be summarized as numbers and percentages and continuous variables as means and standard deviations, minimum, and maximum.

Following this, intention-to-treat analysis will be performed only for the primary outcome, and then performing multiple imputation with a sensitivity analysis using both observed and imputed data. *P* values of < 0.05 will be considered significant.

Statistical analysis will be conducted using R Statistics software. The stress reactivity outcome variables were measured only at T0 and T1. HRV is a primary outcome that is a continuous dependent variable. We will analyze our data using repeated measures analysis of variance (ANOVA) to examine the interaction between time (pre-post intervention), within-subject factor, and the between-group factor treatment group. This analysis allows us to compare the two groups over time to examine whether participants in the EMD condition benefit more in terms of stress reduction, when compared to the retrieval-only condition, from baseline to post-treatment.

We will analyze the secondary outcomes (self-report and neurocognitive measures) using linear mixed models, with a random effect for participants. Data from time points T0, T1, T2, and T3 will be included in the repeated measures models. In all analyses, a treatment × time interaction term will represent the effect of EMD and EMD retrieval-only interventions of the outcome variables over time. Trauma type, gender, and age will be included as covariates in all models, both for the primary as well as the secondary outcome(s).

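### Intention-to-treat is confined to the primary outcome, HR and PEP are left without it or any imputation, and the lead HRV analysis is not named

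*Protocol article*

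**What the plan says.** Two sections of the protocol article speak to who is analysed.

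- **Statistical analysis:** "intention-to-treat analysis will be performed only for the primary outcome", and the sentence continues "and then performing multiple imputation with a sensitivity analysis using both observed and imputed data". HRV is tested by repeated-measures ANOVA through the time-by-group interaction. On timing: "The stress reactivity outcome variables were measured only at T0 and T1". For the rest: "We will analyze the secondary outcomes (self-report and neurocognitive measures) using linear mixed models, with a random effect for participants", using T0 to T3.
- **Data collection, quality control, and confidentiality:** "All randomized participants will be included in the intention to treat analysis". That sentence closes a paragraph under which participants who leave the intervention stay in follow-up unless they withdraw consent. Participants reluctant to do the full assessment are asked for the PCL-5, PSS, HSCL-25, WHOQOL-BREF, CVLT, Digit Span and TMT. All of these are secondary measures; HRV is not on the list.

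**The concern.** The word 'only' is a stated rule, not an omission. It denies intention-to-treat to every secondary outcome and puts no other analysis population in its place. A per-protocol analysis of PTSD symptoms, quality of life or cognition would comply with it. That matters because the Discussion rests its interpretation partly on neurocognitive function and on PTSD symptoms up to 3 months.

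The second difficulty is the model. A two-time-point repeated-measures ANOVA on observed data needs both T0 and T1. Unless values are imputed, a participant without a T1 recording contributes nothing. For HR and PEP nothing in the plan prevents this. For HRV imputation is planned, but its rank is not given, so two HRV results could each be read at the 0.05 level and the headline chosen afterwards.

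If loss is related to outcome and differs by arm, a comparison of completers is no longer the randomised comparison.

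**Working it through.** **1. Inputs.** From Sample size: alpha 0.05, power 0.90, correlation ρ = 0.4, f = 0.2, two groups, m = 2 time points, N = 82 (41 per arm), 25% allowance, 110 in total (55 per arm). Time points and models come from Statistical analysis; the reduced assessment comes from Data collection.

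**2. The plan's own figures.** For the group-by-time interaction, λ = N·m·f²/(1 − ρ) = 82 × 2 × 0.04 / 0.6 = 10.93, with 1 and 80 degrees of freedom. Power is 0.904, and N = 80 falls short of 0.90. Inflation: 82/0.75 = 109.3, rounded up to 110; per arm 41/0.75 = 54.7, rounded up to 55. Both figures reproduce. The inflation therefore expects 110 − 82 = 28 randomised participants without analysable data.

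**3. Coverage by outcome.**

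| Outcome | Time points | Model | Intention-to-treat | Imputation |
|---|---|---|---|---|
| HRV (RMSSD) | T0, T1 | Repeated-measures ANOVA | Yes | Planned; lead result not stated |
| HR, PEP | T0, T1 | Not named; apparently the same ANOVA | Excluded by 'only' | None assigned |
| Self-report, neurocognitive | T0–T3 | Linear mixed model, random participant effect | Excluded by 'only' | None assigned, but the model keeps partial data |

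**4. The two statements side by side.** One says who enters the intention-to-treat analysis; the other says for which outcome it is done. Formally both can be true. In context they pull apart: the paragraph that promises inclusion of everyone has just arranged to collect secondary measures from non-adherent and reluctant participants, and these are the outcomes from which the other section withdraws intention-to-treat.

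**5. Number analysed if completers lead.** Only the 25% row uses a document figure; the other rates are assumed.

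| Loss | Completers of 110 | Omitted | Power |
|---|---|---|---|
| 0% | 110 | 0 | 0.967 |
| 10% | 98 | 12 | 0.947 |
| 20% | 88 | 22 | 0.923 |
| 25% | 82 | 28 | 0.904 |
| 30% | 76 | 34 | 0.881 |
| 40% | 66 | 44 | 0.832 |

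At the planned loss, power holds. The issue is bias, not sample size.

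**6. Possible bias, on assumptions.** The documents give no arm-specific or outcome-related dropout figure.

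- *Simple arithmetic:* bias = share lost × outcome gap between those lost and completers. Assume 25% loss, a gap in one arm only, and no imputation. Gaps of 0.25, 0.5 and 1.0 SD give 0.06, 0.125 and 0.25 SD, or about 16%, 31% and 63% of the target d = 0.4.
- *Simulation* (4,000 trials, 55 per arm, correlation 0.4, no true effect, about 25% loss): with loss completely at random, the completer analysis has bias of about 0.00 SD and rejects in 4.9% of trials. With loss depending on baseline HRV in opposite directions by arm, a deliberately adverse assumption, completer bias is 0.26 SD and the false-positive rate 20%. A regression imputation by arm on all randomised participants, standing in for multiple imputation, has bias of about 0.00 SD in the same setting.

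**The case against.** **The plan does include imputation.** A reader who stops at the word 'outcome' might infer that the HRV headline rests on completers. The documents do not establish that. The sentence goes on to plan multiple imputation, and ANOVA on imputed data would keep all randomised participants. What stands is that the lead result is not named. An analysis plan that is not shown might settle this, but it would first have to overrule the word 'only' for the other outcomes.

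**The secondary outcomes use mixed models.** It is tempting to call them completer analyses. They are not: these models keep participants with partial follow-up, and no completer or per-protocol set is defined anywhere. But a mixed model does not decide who belongs to the analysis set or whether people are analysed as allocated. Nor does it reach HR and PEP, which are neither self-report nor neurocognitive.

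**Nausea as arm-specific loss.** The plan's example of a reason for withdrawal is that "the participant feels nauseous doing eye movements task when recalling the memory", and controls make no eye movements. A reader might infer planned differential loss of T1 data. The withdrawal is from the intervention, however, and such participants go on to follow-up unless they withdraw consent. It signals a risk, not missing data. The Randomization section also offers people who refuse the follow-up assessment the primary outcome alone, but this follows the T2 and T3 schedule, when HRV is not measured, so its bearing on T1 is unclear.

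**Covariance.** The phrase "an unstructured covariance model is assumed" might be read as fixing the T0 to T3 models. It belongs to the two-time-point power calculation; the longer models are specified with a random participant effect. No change of covariance structure follows from it.

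**Contradiction.** A reader might call the two intention-to-treat statements flatly contradictory. As they can be reconciled formally, inconsistent in scope is the fair description.

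**Conclusion.** The point holds in limited form. The restriction of intention-to-treat to the primary outcome is an explicit rule that leaves every secondary outcome without a stated population. HR and PEP, assuming they fall under the ANOVA as the text suggests, would lose anyone without T1. For HRV a completer headline of about 82 of 110 is possible but not established.

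The size of any bias cannot be derived from the documents. It is zero if loss is completely at random, and about a quarter of an SD under adverse assumptions that no document figure supports. The case for change rests on the stated rule and the unnamed lead analysis, not on those figures.

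**What to change.** - In Statistical analysis, delete 'only' and state that every outcome is analysed in all randomised participants according to allocated arm. Make the data collection section agree.
- For HRV, HR and PEP, name one all-randomised analysis as primary: either multiple imputation carried out by arm, or a likelihood-based mixed model with T0 and T1. Make the complete-case ANOVA the sensitivity analysis.
- Keep the planned mixed models for the T0 to T3 outcomes, fitted to all randomised participants.

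The cost is wording and modest programming. No new data are needed and the sample size does not change. The text should be settled before allocation is revealed to the statistician.
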